### Ethics approval and consent to participate

The study protocol was approved by the Sud Est 4 Ethics Committee on October 18, 2016 and cover all sites involved in this study. The research carried out will be on accordance with the Helsinki Declaration and ICH GCP Guidelines. The study complies with the principles of the data protection act in France. Each GP had to collect a writer consent at the beginning of the procedure. This consent is retained in the CRF. The patient can stop the study at any time with an oral information at his GP.

## Discussion

The majority of studies are based on non-pharmacological interventions to prevent mobility impairment. This large-scale randomized trial is a program for older patients screened in primary care. To the best of our knowledge, this will be the first study in France in which a multimodal intervention with cooperation between geriatricians, general practitioners, dieticians, and personal trainers will be implemented.

### Discussion of the study design

The study will be randomized and multicenter, and will investigate the effect of a specific clinical pathway with both the effects of the intervention and, simultaneously, the implementation of the program in current practice conditions, across various areas of France. Rather than an individual randomization, a cluster design was chosen in order to limit the risk of contamination, but also for reasons of feasibility and ethics; it would have been difficult to justify why two different patients in the same practice would not have access to the same management. Likewise, we chose to stratify randomization to ensure that GPs working in the same practice would be randomized to the same group. The high number of clusters (60 in total) and low number of patients within each cluster should help reduce the risk of bias due to intra-cluster correlation.

Despite the cluster design, the effects of the intervention will be determined individually. An open-label design is necessary given the nature of the intervention. The effects of the intervention will be evaluated using an objective outcome, the SPPB, which has shown to be reproducible [29, 39]. An SPPB score below 10 is predictive of all-cause mortality [42] and reveals a weakness of lower extremity function and higher mobility disabilities [43]. Clinically, an improvement of one point in the SPPB score is associated with substantial and clinically relevant changes in physical performance [44]. SPPB is a reliable tool to screen for patients likely to benefit from a physical exercise program [41] and it is generally considered as a valid predictive tool to assess physical performance and predict risk of mobility loss [11, 39, 42]. The GPs will screen systematically each consecutive patient over 70 years of age to limit selection bias. Furthermore, they will note each refusal to participate in order to evaluate the acceptability of the program from the patients’ perspective.

Standard training will be provided to the participating GPs for the recruitment and to physical trainer to ensure harmonized delivery of information. All GPs will be given specific training in group sessions for the loss of mobility screening assessment, prior to randomization. This will ensure that the screening and inclusion procedure is the same for all patients, and ensure comparability between groups for the measurement of the primary outcome. Moreover, GPs in the intervention group will not be involved directly in the intervention itself.

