**Method:**

The PRISME-3P study is a national, interventional, multicenter, cluster randomized trial. Patients over 70 years of age will be systematically screened by their general practitioner (GP) on the basis of clinical criteria of mobility limitation. To avoid contamination bias, the unit of randomization will be the GP practice. In the intervention group, patients will consult a geriatrician and a dietician, and will receive a physical training program from a personal trainer who will demonstrate the exercises and provide follow-up coaching. The control group will receive standard care. The primary outcome will be the change in Short Physical Performance Battery (SPPB) scores between inclusion and 6-months follow-up.

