## Methods

### Study design

PRISME-3P is a national, multicenter, and cluster randomized trial conducted in France (Fig. 1). GPs will be randomly assigned to the intervention group or to the control group. Recruitment and inclusion will be performed by GPs and the intervention will take place at the hospital and home of the patient. The planned inclusion period is 24 months with 12 months follow-up.

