**Fig. 1 Fig1:**
[figure not shown]
Design of the PRISME 3P randomized controlled trial

In both groups, GPs will perform a consultation for inclusion at baseline and two evaluations at 6 and 12 months thereafter. In the intervention group, an initial blood test will be performed (blood cell count, CRP, pre-albuminemia, and albuminemia). Follow-up will include two visits to the allocated study hospital outpatient clinic (within 2 weeks and at 3 months from inclusion) and 3 visits to the GP (at 3, 6, and 12 months from inclusion). All data collected will be notified by the GPS on the case report form (CRF).

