### Participants

All subjects aged over 70 years old will be eligible except patients with functional or locomotor disabilities, a life expectancy less than 6 months, a progressive chronic disease affecting participation in the program, or a MMSE< 20.

For each consecutive patient over 70 years of age without exclusion criteria, GPs will screen patients with medical interview to detect 2 or more inclusion criteria described in Table 1. These criteria are partly derived from the sarc-f screening tool for sarcopenia [28].

**Table 1 Tab1:** Summary of eligibility, inclusion, non-inclusion and exclusion criteria

Eligibility criteria	Inclusion criteria	Exclusion criteria
Difficulty lifting packages over 4.5 Kg	Age > 70	Patient refusal to participate to the study
Difficulty rising from low seats without help of arms	SPPB <10	Functional or locomotor disabilities
Difficulty climbing less than 10 steps of stairs	≥ 2 eligibility criteria	Life expectancy less than 6 months
Difficulty moving or reduced walking speed		A chronic disease affecting participation to the program
Difficulty walking over 400 m without break		MMSE< 20
Walking time less than 1 hour per week		
Feeling of exhaustion during domestic activity		
> 2 falls during the last year		
Involuntary weight loss (> 5% in 1 month or > 10% in 6 months)		

In the presence of 2 or more inclusion criteria, GPs will assess the patient using the Short Physical Performance Battery (SPPB) [29]. In the event of a SPPB score < 10 (out of 12), patients will be given 9 questionnaires grouped in a unique folder: Activity Scale for the Elderly (PASE) [30], weekly sedentary time inspired by Gardiner [31], Activity of daily living scale (ADL), Instrumental activities of daily living scale (IADL) [32], SF-12 scale [33], Mini-Nutritional Assessment (MNA) [34], EPICES score *(Evaluation de la précarité et des inégalités de santé dans les centres de santé (in French))* [35, 36], Charlson index [37], Geriatric Depression Scale (GDS) [38] (Table 2) that measure their autonomy, nutrition and physical activity, and will be proposed another medical appointment for inclusion in the study. If a patient refuses to participate in the study, this will be noted in the CRF.

**Table 2 Tab2:** List of questionnaires

List of questionnaires	
Physical activity	Activity Scale for the Elderly (PASE) [30]
	Weekly sedentary time inspired by Gardiner [31]
Autonomy	Activity of Daily Living scale (ADL)

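### GPs enrol patients with their practice's arm evidently known, and the named primary model does not adjust the 6-month effect for any resulting gap in baseline SPPB

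*Protocol article*

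**What the plan says.** All places are in the Protocol article.

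- **Unit of allocation.** Abstract, Method: "To avoid contamination bias, the unit of randomization will be the GP practice".
- **Who enrols, and for how long.** Study design: "Recruitment and inclusion will be performed by GPs and the intervention will take place at the hospital and home of the patient". The same section adds: "The planned inclusion period is 24 months with 12 months follow-up".
- **When the arms part.** In the text after Figure 1, intervention patients attend the hospital clinic "within 2 weeks and at 3 months from inclusion".
- **What the GP decides.** Under Participants and Table 1, the GP conducts the screening interview, applies the exclusions and administers the SPPB, which must be below 10 for entry. One exclusion is "a progressive chronic disease affecting participation in the program". Under Ethics approval, the GP also obtains consent.
- **Blinding.** Discussion of the study design describes the trial as open label.
- **Safeguards.** The same section states "The GPs will screen systematically each consecutive patient over 70 years of age to limit selection bias" and has each refusal noted, in order to judge acceptability. It also states "All GPs will be given specific training in group sessions for the loss of mobility screening assessment, prior to randomization", and treats this as securing a uniform procedure and comparable groups.
- **Analysis.** Under Statistical analyses, Primary outcome, the main model has a random GP effect, with intervention, period and their interaction as fixed effects, and is adjusted for center and age at inclusion. An interaction of SPPB at inclusion with intervention is added to test effect modification.

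**The concern.** Randomising practices makes the practices comparable. It protects a comparison of patients only if the patients are identified, or the recruiter is kept unaware of the arm, independently of the allocation. Here the person who judges eligibility, scores the qualifying test and discusses consent is the GP whose practice was allocated.

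The pressures on that GP differ by arm. An intervention patient is asked to make hospital visits and exercise five days a week; a control patient continues standard care. The article's Feasibility section itself notes that the hospital setting may limit acceptability and that trust in the GP may help it. The GP-scored SPPB also serves two purposes: it decides entry, and it is the baseline of the primary outcome. Borderline scoring can therefore affect both who enters and how much change is recorded.

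At stake is whether the 6-month difference can be attributed to the program. The bias could run in either direction, and a larger number of clusters would not reduce it.

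**Working it through.** **Step 1: the sequence.** No passage says outright that patients are included after their practice is allocated. It follows from three statements read together. Inclusion runs for 24 months. Each intervention patient has a hospital visit within 2 weeks of his or her own inclusion, and controls have none. The design is open label. Once a GP's first patient has been sent to the hospital, or has not, that GP knows the arm while still enrolling the rest of the planned five.

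**Step 2: what each safeguard reaches.**

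| Safeguard | What it controls | What it leaves open |
|---|---|---|
| Common training before randomisation | Technique and knowledge of the criteria | Knowledge of the arm at enrolment |
| Consecutive screening | Who is approached | Exclusion by judgement, scoring near the cut-off of 10, persuasion |
| Recorded refusals | Visibility of refusal | Exclusions; no comparison by arm is stated |
| Baseline tables by group and a table of clusters | Visibility of measured imbalance | Removal of that imbalance; unmeasured factors |

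**Step 3: does the model remove a measured baseline gap?** The intervention-by-period coefficient is the between-arm difference in mean change. With both visits complete, a covariate that is constant across a patient's visits (age, center, SPPB at inclusion, or SPPB at inclusion times intervention) is orthogonal to that within-patient contrast and leaves the coefficient unchanged. I checked this on one simulated data set of 60 GPs with 5 patients each: the coefficient was 0.263 with no covariates and 0.263 after each was added. So, as written, a baseline SPPB gap stays in the estimate. If the change score is instead modelled with one row per patient, the article names the SPPB-by-intervention term but no SPPB main effect.

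**Step 4: size of the bias, as an illustration.** Assumptions, none of them from the article: a baseline gap g = 0.5 SPPB points, equal variances at both visits, a baseline-to-6-month correlation r of 0.4 to 0.7, and selection acting through the recorded baseline score. With no treatment effect the expected 6-month gap is r × g, so the gap in change has size g − r × g = (1 − r) × g.

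- r = 0.7: 0.3 × 0.5 = 0.15 points; 0.15/0.8 = 19% of the target.
- r = 0.4: 0.6 × 0.5 = 0.30 points; 0.30/0.8 = 38% of the target.

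**Step 5: what such a shift does to the test.** First the plan's own figure (Sample size calculation: difference 0.8, 5 patients per GP, ICC 0.15, SD 1.7, power 80%). A two-sided alpha of 0.05 is my assumption.

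- Design effect: 1 + (5 − 1) × 0.15 = 1.6.
- Reading 1.7 as the within-GP SD, total SD = 1.7/√(1 − 0.15) = 1.844.
- Clusters per arm = 2 × 1.844² × (t quantiles for alpha and power)² × 1.6/(5 × 0.8²) = 27.7, which rounds up to the stated 28.
- At 30 GPs per arm, SE = 1.844 × √(2 × 1.6/150) = 0.269.

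Noncentral t, 58 degrees of freedom:

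| Shift from selection alone | Error rate with no true effect | Power if the shift opposes the intervention |
|---|---|---|
| 0 | 5.0% | 83.2% |
| 0.15 | 8.5% | 66.0% |
| 0.30 | 19.5% | 44.7% |

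**The case against.** The strongest reply is that the article recognises selection bias and acts on it. Screening is consecutive, refusals are logged, training covers the eligibility criteria and precedes randomisation, baseline tables by group and by cluster are promised under cluster-trial guidelines, and intervention GPs do not deliver the program. Much of entry is structured: a list of complaints, an MMSE limit and a performance test described as reproducible. All of this stands as mitigation. None of it conceals the arm, so it does not support an unqualified assurance.

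It is also fair that the size in the working is hypothetical. Entry is truncated at SPPB below 10, which makes equal variances doubtful, and no document gives r or a baseline gap.

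Four stronger readings are tempting and are not supported:

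- *The article states that only training precedes randomisation.* It states that training does; the order of the rest is inferred, though firmly.
- *The program-related exclusion has meaning only in the intervention arm.* Control GPs are trained on the criteria and the study organisation and can judge it. Different use by arm is possible, not inherent.
- *The arms will differ.* The documents show only that they can.
- *Waiting for a practice's patients before releasing its arm would be quick, given the mobility limitation of almost 30% in the Background.* That figure is for people over 65. It is not the share of those over 70 with at least two criteria, an SPPB below 10 and no exclusion.

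**Conclusion.** The point holds in a limited form. GPs evidently know their arm while they screen, exclude, score and obtain consent, and the stated safeguards reduce recruitment bias without concealing allocation. The claim that training secures an identical procedure and comparable groups is too strong. Nor does the primary model, as described, remove a measured baseline SPPB gap from the 6-month effect.

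The 0.15 to 0.30 points (19% to 38% of the target) indicates scale under the stated assumptions; it does not estimate what will happen. Baseline adjustment deals with imbalance in the recorded score. It does not deal with unmeasured differences such as motivation.

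**What to change.** 1. **Statistical analyses, Primary outcome.** Make the primary 6-month comparison a model with one row per patient: 6-month SPPB, or its change, on arm, center, age and SPPB at inclusion as a main effect, with a random GP effect. Report the SPPB-by-intervention interaction as a separate effect-modification analysis. State that unmeasured differences remain. SPPB at inclusion is already collected, so the cost is wording, and precision should improve.
2. **Reporting.** Tabulate screened, excluded (by reason), refused and included patients by arm and by cluster. Refusals are already recorded; numbers screened and reasons for exclusion need a screening log. The cost is small.
3. **Discussion of the study design.** Replace the assurance drawn from training with a statement that training standardises the procedure and that a risk of selection after allocation remains.

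Holding back a practice's allocation until its patients have consented and been assessed at baseline would address the cause, but it is an option only where it can be reconciled with visit times counted from inclusion. It is not costless. If a GP's five patients arrived evenly over 24 months (an assumption), they would be 24/5 = 4.8 months apart, and the first would wait 4 × 4.8 = 19.2 months for the fifth. Practices with several GPs are one sampling unit and would need more patients before release.

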### Feasibility

Patients with an estimated life expectancy of less than 6 months will be excluded as they would derive no benefit from intervention. In France, patients choose their GP and generally trust him/her. We believe this privileged relationship might help acceptance and adherence to the program, and also limit the rate of patients lost to follow-up. Conversely, part of the intervention will take place in a hospital setting and this might limit the acceptability of the program. This was decided for feasibility reasons, as this limited the number of personal trainers required and helped to optimize their time by avoiding multiple home visits.

The recruitment of patients from primary care will be facilitated by the collaboration and institutional support of the university general practice departments in each participating area. To facilitate GP adherence and acceptability of a screening, GP needs a valid, simple and rapidly administered tool. The FRASI-Study found that the use of SPPB is feasible in daily practice in primary care [45]; it is a simple tool that has good performance to predict incident ADL disability, worsening mobility, and death [39, 43, 46]. We have estimated the time required to deliver the SPPB to be less than 20 min, which corresponds to the mean duration of a regular GP consultation in France. To minimize the duration of the inclusion visit, GPs will screen and assess patients and give them a questionnaire during a routine visit. They will be invited to read this questionnaire and answer the questions to the best of their abilities, which will be then completed with the help from GPs during a dedicated inclusion visit.

To the best of our knowledge, this will be the first study in France in which a multimodal intervention with cooperation between geriatricians, general practitioners, dieticians, and personal trainers will be implemented. We will be able to evaluate the implementation of a collaborative program that may help setting-up effective pathways for prevention of loss of mobility in primary care.

## Abbreviations

ADL: Activity Daily Life
BMI: Body Mass Index
EPICES: *Evaluation de la Précarité et des Inégalités de santé dans les Centres d’Examens de Santé* (in French)
GDS: Geriatric Depression Scale
GP: General Practitioner
IADL: Instrumental Activity Daily Life
MAPA: Monitor of Adapted Physical Activities
MMSE: Mini Mental State Examination
MNA: Mini Nutritional Assessment
PASE: Physical Activity Scale for the Elderly
PRISME-3P: Elderly Patient at RISk of loss of Mobility, Exercise – Primary care, Prevention, care Pathways
SPPB: Short Physical Performance Battery
